**Part I 1(c): Abstract of Research Comprehensible to a non-specialist**

**Background:** Sleep disturbances are highly prevalent in ageing population and patients with age-related neurodegenerative diseases, which severely affect cognition and even lead to accumulated amyloid- $\beta$  ( $A\beta$ ). At present, non-pharmacological interventions for sleep disturbances in dementia patients are accepted as first line of treatment, of which the evidence from clinical trials is very limited. Encouraging results from recent studies on transcranial direct current stimulation (tDCS) showed moderate positive effects on sleep quality in preclinical Alzheimer's disease (AD). Compared to tDCS, high-definition transcranial alternating current stimulation (HD-tACS) enables the entrainment of neuronal activities with optimized focality through injecting small electric current with a specific frequency and has significant enhancement effects on slow wave activities.

**Objectives:** We aim to 1) investigate and compare the safety, efficacy and sustainability of 40 Hz HD-tACS and HD-tDCS over left dorsolateral prefrontal cortex (DLPFC) in mild neurocognitive disorder due to AD (NCD-AD) patients with sleep disturbances; 2) examine the relationship between the changes in sleep quality, cognitive function and saliva  $A\beta$  levels.

**Design:** A 4-week randomized, double-blind, sham-controlled trial.

**Methods:** Chinese right-handed mild NCD-AD patients with sleep disturbances (aged from 60 to 90 years) will be randomly assigned to a 4-week intervention of either HD-tACS, HD-tDCS, or sham HD-tCS, with 33 participants per arm. Before intervention, structural magnetic resonance imaging (MRI) data is used to construct individual realistic head model. Comprehensive assessments, including sleep quality, cognitive performance and saliva  $A\beta$  levels will be conducted at baseline, 4th week, 8th week, 12th week and 24th week. Program adherence and adverse effects will be monitored throughout intervention.

**Data analysis:** The primary outcomes will be the changes in sleep quality and memory performance with modality-driven paradigms (HD-tACS, HD-tDCS, sham HD-tCS), and comparisons of group differences across different time points. Secondary outcomes will be the changes objective sleep pattern, global cognition, saliva  $A\beta$  levels and quality of life. Intention-to-treat analysis will be carried out. Changes of efficacy indicators from baseline to each follow up point will be tested with mixed effect model.

**Significance:** This study aims to investigate the feasibility, safety and efficacy of HD-tACS and HD-tDCS over left DLPFC for sleep disturbances and cognitive dysfunction in mild NCD-AD patients. It will also test the program adherence, tolerability and adverse effects of this innovative neurotechnology. Information will be helpful for in-depth understanding the relationship of "sleep disturbances-amyloid deposition" and guiding the further studies of sleep medicine and neurodegenerative diseases.

**Part II 1 (a): Project Objectives**

To investigate the effects of a 4-week 40 Hz HD-tACS on sleep quality and cognition in mild NCD-AD patients.

To examine the effects of a 4-week HD-tDCS on sleep quality and cognition in mild NCD-AD patients.

To compare the efficacy and sustainability of HD-tACS and HD-tDCS.

To examine the relationship between the changes in sleep quality, cognitive function and saliva amyloid  $\beta$  levels.

### **Work done by others**

As a common modality of tCS, transcranial direct current stimulation (tDCS) shows positive effects on post-sleep declarative memory in AD patients [10-12]. For instance, tDCS over frontal cortex during sleep could boost the SWA in healthy old adults but showed no positive effects on memory function [13]. In contrast, a clinical trial involved 19 middle-aged patients with insomnia and found no tDCS effects on sleep architecture [14]. To date, only one study with tDCS has been conducted in preclinical AD patients [15]. They found that tDCS can increase the SWA and the sleep-mediated improvement in visuo-spatial memory. The heterogenous results of tDCS effects on sleep quality and sleep-dependent brain function highlight that targeting specific brain oscillations (i.e., SWA) is crucial to achieve optimal benefits [16].

Compared to tDCS, transcranial alternating current stimulation (tACS), as an advanced modality of tCS, delivers frequency-dependent sinusoidal waveform of current that can modulate and monitor the brain activities in a more specific manner [17]. In brief, the proposed mechanism of tACS is hypothesized to be neural entrainment of the cortex that is reflected in neural spike alignment to the externally applied stimulation waveform [18]. Compared to tDCS, tACS with specific frequency is more effective in triggering the

endogenous slow oscillations and enhancing brain function in healthy individuals as well as in patients with brain disorders [16]. For example, tACS over left dorsolateral prefrontal cortex (DLPFC) shows dose-dependent effects on SWA and sleep-dependent memory consolidation [7,19,20]. Importantly, recent encouraging findings showed that gamma-band (i.e., 40 Hz) stimulation can ameliorate Alzheimer's associated pathology ( $A\beta$ ) and have marked effects on cognitive function in aged mice [21,22]. The current findings of tACS effects suggest that ① left DLPFC, as a hub of central-executive network (CEN), not only plays a key role in modulating the sleep-related brain activities, but also involves in high-level brain function (i.e., executive function, memory); ② tACS effects on sleep quality can affect cognition and behavior, but the specificity (i.e., cognitive domains) and neural mechanisms of these changes are not yet well understood.

### **Work done by us**

Our team has completed a randomized clinical trial on the cognitive effects of anodal tDCS combined with cognitive training in mild NCD-AD patients [23]. We found that a 4-week course anodal tDCS has positive effects on cognitive function. The observed tDCS-induced cognitive benefits indicate that cognitive optimization remains possible in preclinical AD. In the secondary analysis, we found that anodal tDCS has moderate positive effects on sleep quality (measured by the Pittsburgh Sleep Quality Index, PSQI).

Compared to combined modality, mild NCD-AD patients who received tDCS only demonstrated prominent enhancement on sleep quality at 12th week (Score change:  $F=9.5$ ,  $p=0.003$ , Cohen's  $d=0.089$ ) (Appendix 1). Within the tDCS group ( $n=62$ ), we defined poor sleepers as baseline PSQI total score  $>5$  and good sleepers as PSQI total score  $\leq 5$  [24]. After a 4-week course tDCS treatment, poor sleepers showed significantly enhanced sleep quality than good sleepers at 4th week ( $t=-2.41$ ,  $p=0.02$ , Cohen's  $d=0.664$ ), 8th week ( $t=-2.7$ ,  $p=0.01$ , Cohen's  $d=0.714$ ) and 12th week ( $t=-4.38$ ,  $p<0.001$ , Cohen's  $d=1.209$ ). Meanwhile, poor sleepers had more cognitive gains than good sleepers across the follow-up observations, including global cognition measured by ADAS-Cog (4th week,  $t=-2.42$ ,  $p=0.019$ , Cohen's  $d=0.669$ ; 8th week,  $t=-2.19$ ,  $p=0.031$ , Cohen's  $d=0.605$ ). Moreover, enhanced sleep quality was prominently correlated with tDCS-induced cognitive benefits (ADAS-Cog:  $r=0.33$ ,  $p=0.029$ , corrected). Our results indicate that a 4-week course tDCS has significant positive effects on sleep quality and cognitive function in mild NCD-AD patients with or without sleep disturbances. Interestingly, the baseline sleep quality is a key factor that has close relationship with intervention-induced cognitive gains. Due to the lack of sham tCS (i.e., controlled group) [23], the potential placebo effects on sleep quality are not known.

Meanwhile, considering the complexity of brain waves, tACS has several advantages than tDCS: 1) Frequency-specific: tACS could generate electric current with a defined phase and frequency, which offers the opportunity to stimulate the brain region with a specific waveform; 2) Focality: the results of our computational modelling has shown that tACS could generate a more focal electric field than tDCS. 3) tACS-induced brain activity changes: stemming from our preliminary data ( $n=3$ ), we found that single session of 40 Hz tACS over left DLPFC could change the brain oscillations (measured by NeuroSky head set) from alpha/beta activities (i.e., normal awake) to theta/delta activities (i.e., slow wave activities).

Collectively, disease-specific sleep pattern dominated by slow-wave activities (i.e., theta and delta activities) can be modulated by weak current, which sheds new light on the therapeutic advantages for sleep disturbances. Particularly, high-definition tACS (HD-tACS) utilizes four small return cathodal electrodes that proficiently limit the spread of current flow and enhance the focality with gamma-band frequency (Appendix 2). Given the very limited therapeutic options for mild NCD patients comorbid sleep disturbances, we aim to conduct a randomized controlled trial (RCT) to examine and compare the safety, efficacy and sustainability of 40 Hz HD-tACS and HD-tDCS in the management of sleep disturbances and cognitive impairments in mild NCD-AD patients.

## **Part II Section 2(b) (i) – Research plan and methodology**

### **Research Plan**

This study adopts the design of a 4-week double-blind randomized controlled trial of 40 Hz high-definition transcranial alternating current stimulation (HD-tACS). It makes reference to the suggested requirements of a phase II design for non-pharmacological intervention. The aims of this study are to explore the acceptability, potential benefits and adverse events of this novel technology. Comprehensive assessments will be conducted at the baseline, 4th week, 8th week, 12th week and 24th week to evaluate the sustainability of enhancing effects on sleep quality and cognition. Secondary outcomes include objective sleep quality, cognitive function profiles, saliva A $\beta$  levels and quality of life.

### **Methodology**

#### Recruitment centers and participants

Participants will be recruited through existing research cohorts, cognitive disorder clinics, and local advertisements at elderly centers in Hong Kong. The research team, including psychiatrists, sleep specialists and neuroscientists, will identify the sleep disturbances and mild neurocognitive impairments (i.e., NCD-AD). Potential participants will be invited to be screened by our trained research assistant to determine the eligibility and availability to participate in the study. Both participants and their caregivers will be briefed about the study before a decision for informed consent.

Potential participants will need to satisfy the following inclusion criteria [25]:

1. Chinese, aged from 60 to 90 years.
2. Mild neurocognitive disorder due to Alzheimer's disease (NCD-AD) is diagnosed according to the *Diagnostic and Statistical Manual of Mental Disorders*, Fifth Edition (DSM-5) [23]. NCD-AD patients are defined by the following criteria: (1) evidence of modest cognitive decline in at least one of six domains of cognition (memory, perceptual-motor, complex attention, language, executive function and social cognition), and with clinical features indicative of AD, identified with the Montreal Cognitive Assessment (MoCA) score range from 22 to 26; (2) no interference with independence in everyday activities; (3) and no better explanation by other psychiatric disorders. NCD-AD patients fulfill the criteria of NCD and have impaired episodic memory assessed by delayed recall.
3. Sleep disturbances are defined as a Pittsburgh Sleep Quality Index (PSQI) total score above 5 [24].

Exclusion criteria include:

1. Previous diagnosis of other major neurocognitive disorders; 2. Past history of bipolar disorders or psychosis; 3. Physically frail affecting attendance to training sessions; 4. Already attending regular training, such as cognitive behavioral therapy; 5. Taking a psychotropic or other medication known to affect cognition (e.g. anti-dementia medication); 6. Significant communicative impairments. 7. History of major neurological deficit including stroke, transient ischemic attack or brain tumor.

### **Pre-intervention magnetic resonance imaging**

High-resolution structural MRI (sMRI) scans will be collected at the Prince of Wales Hospital using a 3.0 Tesla Philips Achieva scanner (Philips Healthcare, Best, Netherlands) within a single session during which cushioning and a thermo-plastic face mask were employed to minimize head movements. T1-weighted magnetization prepared rapid gradient echo (MPRAGE) sequence is used to optimize the grey-white contrast, with the following parameters [26]: axial acquisition with a  $256 \times 256 \times 192$  matrix, thickness = 1 mm, no gap, field of view (FOV) = 230 mm, repetition time (TR) = 2070 ms, echo time (TE) = 3.93 ms, flip angle =  $15^\circ$ . The sequence yields high quality isotropic images with the voxel size of 1 mm  $\times$  1 mm  $\times$  1 mm. All sMRI scans will be imported to BrainSuite 14.0 (<http://brainsuite.org/>) for surface-based mapping. Surface-based measures include cortical thickness and folding are used as morphometric markers to precisely locate the stimulation target and predict the treatment response [27].

### **Intervention schedule**

This trial is a 4-week intervention with three sessions per week, 20 minutes per session. All participants will receive a total of 12 sessions of interventions. The schedule for intervention is the same in three randomized groups.

### **Intervention strategies**

#### **Apparatus and setting**

High-definition transcranial current stimulation (HD-tCS) is delivered by a battery driven direct current stimulator (DC-Stimulator Plus, NeuroConn, Ilmenau, Germany) through a central anodal electrode surrounded by four return cathodal electrodes (Appendix 2). The base diameter of HD-tCS electrode is 2.4 cm. We place the center electrode (i.e., anodal) over left DLPFC (i.e., F3 according to the international 10-20 EEG system) as in previous studies that investigated the transition from awake to sleep [19,20], and place the return electrode around left DLPFC. The computational head model shows that a central anodal electrode surrounded by four return cathodal electrodes can enhance the focality of current stimulation (Appendix 2). To ensure the electrodes are secured in place, the locations of the electrodes will be measured and positioned based on individual structural MRI. The electrodes are fixed with conductive paste (Ten20®, Neurodiagnostic Electrode Paste, Weaver and Company, Aurora, CO, USA). Participants are instructed to relax during the setting up of transcranial current stimulation.

#### **Stimulation modalities**

##### **High-definition transcranial alternating current stimulation (HD-tACS)**

The stimulation parameters of HD-tACS include: 20 minutes at 40 Hz, 2 milliamps [20].

### **High-definition transcranial direct current stimulation (HD-tDCS)**

The stimulation parameters of HD-tDCS include: 20 minutes at 2 milliamps, 20 seconds fade-in and 20 seconds fade-out [23].

### **Sham transcranial current stimulation (HD-tCS)**

In sham condition, the stimulation only last for 30 seconds with the electrodes left in place for a further 20 minutes. This procedure mimics the transient skin sensation of tingling induced by active HD-tACS and HD-tDCS without producing any sustainable effects [23].

### **Group assignment (Appendix 3)**

All eligible participants will receive a total of 12 successive sessions of tCS intervention. According to the modalities of tCS intervention, the participants will be randomly assigned to three groups:

1. HD-tACS
2. HD-tDCS
3. Sham HD-tCS

### **Randomization**

This is a double-blind sham-controlled randomized clinical study. The assessors and the participants for clinical outcomes will be blinded to the modalities of intervention. Independent research assistants who collect the inventory for cognitive decline will be blinded and will not participate in other outcome assessments.

### **Outcome assessments**

#### **Primary outcomes**

1. Sleep quality: The Pittsburgh Sleep Quality Index (PSQI), as a 19-item self-report questionnaire is used to evaluate the subjective sleep quality in a month [24]. The items produce seven component scores including subjective sleep quality (component 1, C1), sleep onset latency (component 2, C2), total sleep duration (component 3, C3), sleep efficiency (component 4, C4), sleep disturbances (component 5, C5), use of sleep medication (component 6, C6), and daytime dysfunction (component 7, C7). The subscore of each component ranges from 0 to 3, and the maximum total composite score of the PSQI is 21. The sum of these component scores yields a measure of global sleep quality. The cutoff score of poor sleep quality is 5 or more. This Chinese version of the PSQI has been validated with adequate reliability in cognitively intact elderly and dementia patients [29].
2. Memory function:  
Delayed recall of the words: Word-list learning test (WLLT), consisting of sixteen semantically non-associated words that is presented consecutively over three free trials of immediate recall, a 20-min delayed recall (to prevent recency effects) [23,28].

## Secondary outcomes

1. Global cognition is measured by Montreal Cognitive Assessment Hong Kong version (HK MoCA), which is validated global assessment sensitive to detect early cognitive dysfunction in neurocognitive disorder [23].
2. Complex attention is measured by attention network test (ANT). The ANT paradigm ([https://www.sacklerinstitute.org/cornell/assays\\_and\\_tools/ant/jin.fan/](https://www.sacklerinstitute.org/cornell/assays_and_tools/ant/jin.fan/)) is run by E-Prime 3.0 software [32]. Within ANT paradigm, there are four types of cue: no cue, center cue, double cue, and spatial cue; and three types of flanker: neutral, congruent, and incongruent. In a given trial, a central cross-fixation point presents for 400 to 1,600 ms (randomized), subsequently is replaced for 100 ms by one of four warning cues. The target, a central arrow could appear above or below the cross-fixation and is surrounded by two flankers on each side.
3. Executive function is measured by category verbal fluency test (CVFT). On each trial, the participants will be asked to overtly generate words in the animal category, fruit category and vegetable category as many as possible within 60 seconds. The total number of correct words is used to measure executive function [23].
4. Saliva A $\beta$ 40 and A $\beta$ 42 levels: For each individual, saliva samples will be collected at a consistent time of day to avoid circadian effects and will be kept on ice during the collection. The levels of A $\beta$ 40 and A $\beta$ 42 in the saliva samples will be quantified by enzyme-linked immunosorbent assay (ELISA)-type assays (Aurin Biotech, Inc.) [33]. Each sample will be analyzed in duplicate.
5. Quality of life and everyday functioning are measured by activities of daily living scale (ADL) [26].

## **Assessment schedule**

The comprehensive assessments, including sleep quality, cognitive function, saliva A $\beta$  levels, adverse events and quality of life, will be conducted at 1 week before intervention (baseline, T0), and at 4th week (T1), 8th week (T2), 12th week (T3) and 24th week (T4).

## **Statistical Analyses**

The data analyst will be blinded to the grouping of participants. Analyses will be on an intention-to-treat basis. Linear mixed models will be used to assess the differences between conditions on the primary and secondary outcome measures at each time point. This statistical method will facilitate inclusion of participants with missing data. Intervention, time points, and their interaction will be modelled as fixed effects. Participants will be modelled as random effects at time points. Pre-intervention sleep quality and cognitive profiles will be compared between four randomized groups. Score changes of sleep quality, memory and cognitive performance from baseline to follow-up points across randomized groups will be tested with occasions (time points) at level one and participants at level two. Covariates identified from baseline differences will be entered in the regression model. Secondary analyses of group differences in outcome of domain-specific function, and association between changes of PSQI with neurocognitive function will be performed. We will also monitor the incidence of adverse events and characteristics of program adherence. Statistical significance will be set at 2-sided  $p < 0.05$ . Computations will be performed using R Studio (version 1.1.456).

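### Two unranked primary outcomes are compared between three arms at four visits at 0.05, with no primary visit, contrast or testing order; a false result favouring active over sham has a chance of about 18-25% if the tests are pairwise and unadjusted

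*Protocol*

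**What the plan says.** The abstract's data-analysis paragraph names two primary outcomes without ranking them: "The primary outcomes will be the changes in sleep quality and memory performance with modality-driven paradigms". It also makes "comparisons of group differences across different time points" part of the primary definition. The Outcome assessments section identifies the two measures as the PSQI and 20-minute delayed recall on the word-list learning test.

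The Assessment schedule sets four post-baseline visits, at weeks 4, 8, 12 and 24. There are three arms: HD-tACS, HD-tDCS and sham. One project objective is the active-versus-active question: "To compare the efficacy and sustainability of HD-tACS and HD-tDCS".

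The Statistical Analyses section says "Linear mixed models will be used to assess the differences between conditions on the primary and secondary outcome measures at each time point". The model has fixed effects for arm, visit and their interaction. On error, it says only "Statistical significance will be set at 2-sided" p<0.05. The protocol states no primary visit, primary contrast, order of testing or division of alpha. Sample Size Estimation takes its planning values from week 12 and concerns the PSQI alone, but does not make week 12 the primary visit.

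**The concern.** A protocol should state which outcome, at which time and against which comparator, decides whether the treatment worked. Here the text offers two outcomes, four visits and up to three pairs of arms, all under one nominal 0.05. A difference on either primary outcome at any visit could be presented as a primary result, and the choice could be made after the data are seen. At stake is the meaning of a p-value below 0.05 on a primary outcome.

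**Working it through.** **The plan's own figures.** The protocol gives no overall error rate to reproduce; its only related figure is the sample size.
- Dropout: 28/(1 - 0.15) = 32.9, so 33 per arm, as stated.
- Planning values (week 12): 5.364 (SD 1.5), 5.625 (SD 1.13) and 6.2 (SD 1.3). The pooled SD is sqrt((1.5² + 1.13² + 1.3²)/3) = 1.319. The SD of the three means is 0.349, so Cohen's f = 0.349/1.319 = 0.265.
- A one-way comparison at a single visit needs 47 per arm for 80% power.
- A repeated-measures between-group test, with an assumed correlation of 0.5, needs 29 per arm (five measurements) or 30 (four).

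The stated 28 is therefore close to one overall PSQI test across time. It does not correspond to separate tests by visit and outcome.

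**Number of comparisons.** From the protocol: 2 outcomes x 4 visits x 3 pairs = 24. Active versus sham only: 2 x 4 x 2 = 16. One three-group test per visit and outcome: 2 x 4 = 8.

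**Chance of at least one false result under no effect.** If tests were independent, this would be 1 - 0.95^k. They share arms and participants, so I used simulated null trials (40,000 per setting): normal arm means, equal correlation between visits, a common correlation between outcomes, and a critical value of 1.96 (chi-square on 2 df for the three-group test). The correlations are assumptions, because the protocol gives none: 0.5-0.8 between visits and 0-0.3 between outcomes, with 0.3 between visits as a sensitivity case.

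| Reading of the per-visit tests | Tests | If independent | Visit correlation 0.5-0.8 | Visit correlation 0.3 (upper) |
|---|---|---|---|---|
| Any pair, either direction | 24 | 1 - 0.95^24 = 0.71 | 0.44-0.57 | 0.62 |
| Active v sham, either direction | 16 | 1 - 0.95^16 = 0.56 | 0.35-0.47 | 0.51 |
| Active better than sham | 16, one tail | 1 - 0.975^16 = 0.33 | 0.18-0.25 | 0.28 |
| Three-group test | 8 | 1 - 0.95^8 = 0.34 | 0.21-0.29 | 0.32 |

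If change from baseline is analysed, the correlation between changes is 0.5 whatever the raw correlation, so the results sit at the top of these ranges: about 0.56-0.57 for 24 tests, 0.45-0.47 for 16, and 0.24-0.26 for active better than sham.

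**Benchmarks.** One two-sided 5% test falsely favours active with chance 2.5%; a plan with family-wise control keeps the total at or below 5%. If only one overall test per outcome counted, the figure would be 1 - 0.95² = 0.0975.

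**Power at one visit.** The largest planning gap is 6.2 - 5.364 = 0.836. With SD sqrt((1.5² + 1.3²)/2) = 1.404, d = 0.596. A two-sided t-test with 28 per arm has power 0.591. Baseline adjustment with correlation r raises d to d/sqrt(1 - r²). For an assumed r of 0.5, d = 0.688 and power is 0.715; for r = 0.7, d = 0.834 and power is 0.865.

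**The case against.** Four points can be made for the plan.
- The text never says pairwise. Per-visit tests could be three-group tests, or could depend on the arm-by-visit interaction. This stands, and is why the figures are given by reading. It does not rescue the plan, since every ungated per-visit reading remains several times the nominal level.
- Lists of contrasts and multiplicity adjustment are often left to an SAP, and this one is not shown. This also stands: the figures apply to the protocol as written. But the protocol does address the primary question, and answers it with all visits and both outcomes.
- The Research Plan section describes a phase II-type, exploratory study. That lessens the consequence. It does not remove it, because the protocol also sets a significance level and sizes the trial at 80% power for efficacy.
- The trial is plainly sham-controlled, and the earlier trial's lack of sham is given as a gap. This is correct, and no claim is made here that a comparison with sham is absent.

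A reader might also take the abstract's sentence "Changes of efficacy indicators from baseline to each follow up point will be tested with mixed effect model" to mean that within-arm improvement will count as efficacy, with regression to the mean in a cohort selected on PSQI above 5. The documents do not support that reading. The same paragraph refers to group differences, and Statistical Analyses compares score changes between the randomised groups, so a shift expected equally in every arm cancels.

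**Conclusion.** The point holds. The protocol leaves the primary visit, contrast and testing order open while comparing conditions at every visit on two primary outcomes.

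If the tests are pairwise and unadjusted, a false result favouring an active arm over sham has a chance of about 18-25%. Any nominally significant primary difference has a chance of 44-57% (24 comparisons) or 35-47% (16). Three-group tests give 21-29%. All rest on the assumed correlations; weaker correlation between visits raises them, to about 28%, 62%, 51% and 32% respectively at 0.3.

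A reader might infer that a falsely positive trial is about as likely as not. That goes too far: the figures near one half count sham beating active, and the largest also counts differences between the two active arms. Neither would make this a positive sham-controlled trial.

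**What to change.** Amend the abstract's data-analysis paragraph and the Statistical Analyses section before unblinding.
- Define efficacy as the baseline-adjusted mixed-model difference from sham, either at one named visit or averaged over the follow-up visits. Week 12 supplies the planning effect size; the average is closer to how the trial was sized, but assumes the effect is present throughout.
- Control the error at 0.05 over the two active-versus-sham contrasts and two outcomes by a pre-stated fixed sequence. Naming a visit alone would leave four tests (up to 1 - 0.95^4 = 0.185 if independent). Put PSQI first, because the trial is sized on it, then delayed recall. The order of the two active arms is the sponsor's choice.
- Report the other visits, HD-tACS versus HD-tDCS, and within-arm changes as estimates with confidence intervals.

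The edit is about a paragraph, but the costs should be stated. The other visits and the active-versus-active comparison, itself an objective, become supportive. A later contrast cannot be claimed if an earlier one fails. A single visit with 28 per arm has only about 59% power for the largest planning gap before baseline adjustment, or about 72-87% if the baseline correlation is an assumed 0.5-0.7. An equal split of alpha (0.05/4 = 0.0125) would cost more: by normal approximation, power for one unadjusted contrast falls from 0.61 to about 0.39.

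### The primary model tests score changes and adjusts only for variables that happen to differ between arms at baseline, so it is not fixed in advance and usually gives up the precision of adjusting for the baseline score.

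*Protocol*

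**What the plan says.** All the relevant text is in the protocol; no SAP is at hand.

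- **Outcome variable.** Statistical Analyses: "Score changes of sleep quality, memory and cognitive performance from baseline to follow-up points across randomized groups will be tested". The abstract agrees: "Changes of efficacy indicators from baseline to each follow up point will be tested with mixed effect model".
- **Fixed effects.** "Intervention, time points, and their interaction will be modelled as fixed effects". No baseline-score term is listed.
- **Covariate rule.** "Pre-intervention sleep quality and cognitive profiles will be compared between four randomized groups", and then "Covariates identified from baseline differences will be entered in the regression model". No criterion for a difference is stated and no covariate is named.
- **Number of arms.** The comparison just quoted speaks of four groups, but under Group assignment "the participants will be randomly assigned to three groups".

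No section makes baseline PSQI, baseline word-list recall or any other variable a covariate in its own right.

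**The concern.** A covariate is worth including because it predicts the outcome, not because the arms differ on it. After randomisation any baseline difference is chance, so the rule picks covariates on a criterion unrelated to their value. Two things follow.

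1. The primary model is unknown until the baseline data are compared, and the threshold for that comparison is open.
2. The baseline value of the outcome, normally the most useful covariate, enters only when the arms happen to differ on it. Otherwise the analysis is a plain change score, which is less efficient than adjusting for baseline.

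At stake is power in a small trial planned on 28 evaluable participants per arm.

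**Working it through.** **Inputs from the protocol.** Sample Size Estimation gives week-12 PSQI of 5.364 (SD 1.5), 5.625 (SD 1.13) and 6.2 (SD 1.3); 28 per arm for power 0.8; 15% dropout; 33 per arm and 99 in total. For alpha, Statistical Analyses says "Statistical significance will be set at 2-sided" 0.05. Assessment schedule gives five visits, T0 to T4.

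**Assumptions.** The correlation r between baseline and follow-up is not given, so 0.3, 0.5 and 0.7 are shown. The SD is taken as equal at the two visits. The cut-off for a baseline difference is taken as p<0.05.

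**The plan's own figure.** Pooled SD = √((1.5² + 1.13² + 1.3²)/3) = 1.319, and Cohen's f = 0.265. A repeated-measures ANOVA for the between-group effect (3 groups, 5 visits, assumed between-visit correlation 0.5) needs 29 per group, close to the stated 28. Correlations of 0.3 and 0.7 give 22 and 36. Then 28/0.85 = 32.9, so 33 per arm, and 3 × 33 = 99. The planned size is therefore roughly reproducible, but only with a correlation that the protocol does not state.

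**Variance of the two analyses at one visit.**

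- Change score: 2(1 − r)σ²
- Baseline-adjusted: (1 − r²)σ²
- Ratio, adjusted to change: (1 − r²)/(2(1 − r)) = (1 + r)/2

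**Illustrative power.** The largest planning gap is 6.2 − 5.364 = 0.836. The SD for that pair is √((1.5² + 1.3²)/2) = 1.404, so d = 0.836/1.404 = 0.596. The standardised effect is d/√(2(1 − r)) for the change score and d/√(1 − r²) after adjustment. Power is Φ(effect × √(28/2) − 1.96). At r = 0.5, for example: change score Φ(0.596 × 3.742 − 1.96) = Φ(0.27) = 0.61; adjusted Φ(0.688 × 3.742 − 1.96) = Φ(0.61) = 0.73.

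| r | Variance ratio | Change-score SE larger by | Power at 28 per arm: change → adjusted | n per arm for 80%: change → adjusted |
|---|---|---|---|---|
| 0.3 | 0.65 | 24% | 0.47 → 0.65 | 62 → 41 |
| 0.5 | 0.75 | 15% | 0.61 → 0.73 | 45 → 34 |
| 0.7 | 0.85 | 8% | 0.82 → 0.88 | 27 → 23 |

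The table uses the normal approximation. The t distribution lowers each power by 1 to 2 points (0.59 and 0.71 at r = 0.5; 0.81 and 0.87 at r = 0.7) and leaves the gain unchanged. At r = 0.8 the change-score SE is only 5% larger.

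**Does the protocol's rule recover the loss?** Three arms of 28 were simulated at one visit with the planning means, and the baseline score was entered only if the arms differed on it at p<0.05.

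| r | Power: change score | Power: protocol's rule | Power: always adjusted | Type I error of the rule |
|---|---|---|---|---|
| 0.3 | 0.42 | 0.42 | 0.60 | 0.044 |
| 0.5 | 0.56 | 0.56 | 0.69 | 0.044 |
| 0.7 | 0.80 | 0.80 | 0.85 | 0.045 |

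The rule recovers almost nothing, because the baseline score is flagged in only about 5% of trials.

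**How often the model changes by chance.** With k independent baseline variables each tested at 5%, at least one enters with probability 1 − 0.95^k: 10% for k = 2, 23% for 5 and 40% for 10.

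**The case against.** **The mixed model may already use baseline.** T0 is an assessment point and could be one of the modelled occasions. That does not rescue the plan as written: with free arm means at T0 and complete data, the arm-by-time contrast equals the change-score contrast. Constraining the arms to a common baseline mean would recover the precision, but no such constraint is stated.

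**The details may sit in the SAP.** A protocol that was silent on covariates could be read that way. This one states a rule, and the rule is the problem.

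**The data choose the model, so false positives must rise.** A reader might infer this, but the documents do not support it. Selection uses baseline data only, the protocol blinds the analyst to group, and the simulated type I error is about 0.045. What stands is that the model is not fixed in advance.

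**Baseline PSQI must then enter the memory and cognition models.** The protocol does say that "the baseline sleep quality is a key factor that has close relationship with intervention-induced cognitive gains". But that finding compares poor with good sleepers (PSQI above 5 against 5 or less) within the earlier trial's tDCS group. It concerns gain among treated patients, and everyone in the present trial enters with PSQI above 5, so that contrast does not exist here. It does not make PSQI a required covariate.

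**The numbers rest on assumptions.** This is fair. Neither r nor the cut-off is in the protocol, and the gain is small when r is high. The largest gap at one visit is a convenient case, while the sample size was planned across visits and groups. Restricting entry to PSQI above 5 would lower r but also the baseline SD, so it cannot be used to argue for a larger loss. The direction is more secure: if the baseline SD is k times the follow-up SD, the change-score variance exceeds the adjusted variance by (k − r)²σ², where σ is the follow-up SD, and this is never negative.

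**Conclusion.** The point holds as one of efficiency and pre-specification. The protocol commits to change scores with covariates chosen by chance imbalance, and nowhere secures the baseline value of the outcome. Under equal SDs, adjustment would cut the variance by 35%, 25% or 15% at r = 0.3, 0.5 or 0.7. That is worth roughly 18, 12 or 6 points of power in the illustrative comparison. These are not estimates of this trial's actual power. The statement that baseline is left out in about 95% of trials depends on a p<0.05 criterion that the protocol does not give.

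Inference under the rule remains valid, so this is a change that should be made rather than a fatal flaw. The reference to four groups is a separate slip and adds no weight.

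**What to change.** In Statistical Analyses, delete the sentence on covariates identified from baseline differences and the between-arm baseline comparison that feeds it. State instead that every outcome model adjusts for the baseline value of that outcome whatever the observed balance, by one of two routes:

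- a mixed model on the four post-baseline visits with arm, visit, arm-by-visit, baseline value and baseline-by-visit as fixed effects; or
- a longitudinal model that includes T0 and constrains the baseline means to be equal across arms. This also keeps participants who have only T0 data, in line with the protocol's aim of including those with missing data.

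Name any further covariates in advance. Baseline PSQI in the memory and cognition models is optional. Present baseline data descriptively for the three arms, which also removes the reference to four groups.

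The cost is wording only: sleep quality, cognition, saliva and quality-of-life measures are already scheduled at T0, and the sample size need not change.
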